### Randomisation, allocation and masking

Randomisation by means of a stratified block randomisation procedure will be performed by an independent statistician. Participants will be allocated in a 1:1:1 ratio to the three groups. The size of the randomisation blocks is three. Participants will be stratified according to their baseline habitual protein intake (<0.9 or 0.9–1.0 g/kg aBW/day) and sex to ensure homogeneous distribution of baseline habitual protein intake and sex in the three groups across the two recruitment sites, because there may be a different intervention effect by baseline habitual protein or sex. In case couples are eligible, we will allocate them to the same intervention group to limit interference between intervention groups. We will randomly select on which partner the randomisation for the intervention group is based. Any resulting unbalance in the number of subjects per treatment arm will be corrected in the randomisation of the next block. Due to the nature of the study, researchers, nutritionists and participants are not blinded to the study group.

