### Study timeline

The first clinic visit starts with written informed consent, and when participants are eligible, the baseline assessment will be performed. The baseline assessment consists of questionnaires (frailty status, risk of sarcopenia, self-reported mobility limitations, QoL and healthcare costs) and measurements (physical function, muscle strength and body composition). See below ‘primary and secondary outcomes’ and ‘other measures’ for details on these assessments. An accelerometer will be attached to measure physical activity for 7 subsequent days.

After the baseline assessment, participants will be randomised to one of the three study groups done by the nutritionists and they will inform the participants in which group they are allocated to. Participants randomised to one of the two intervention groups will be invited for a consultation meeting at the clinic to receive their personalise d dietary advice, and personalised advice on optimising the timing of protein intake in close proximity of usual physical activity (intervention group 2 only). This will take place within 2 weeks after the baseline assessment since the personalised advice needs to be composed by the nutritionist. The baseline assessment is considered the start of the study period for participants of the control group, while the consultation meeting is considered the start of the study period for participants of the intervention groups.

One week prior to the 3-month follow-up visit, dietary intake will be assessed again by means of a combination of three food diaries and three 24-hour dietary recalls. The 3-month follow-up visit will take place at the clinic and includes measurement of BW, assessment of self-reported mobility limitations, risk of sarcopenia, QoL, healthcare costs and the accelerometer will be attached to measure physical activity for 7 subsequent days.

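### Correcting couple imbalance in the next block lets unblinded staff foresee which arm that block will lack, a small addition to the predictability of fixed blocks of three

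*Protocol article*

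**What the plan says.** The section Randomisation, allocation and masking fixes a stratified block scheme:

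- Ratio: "Participants will be allocated in a 1:1:1 ratio to the three groups".
- Block size: "The size of the randomisation blocks is three".
- Strata: "Participants will be stratified according to their baseline habitual protein intake (<0.9 or 0.9–1.0 g/kg aBW/day) and sex".
- Couples: "In case couples are eligible, we will allocate them to the same intervention group to limit interference between intervention groups". The index partner is chosen by chance: "We will randomly select on which partner the randomisation for the intervention group is based".
- Repair of the resulting surplus: "Any resulting unbalance in the number of subjects per treatment arm will be corrected in the randomisation of the next block".
- Blinding: "researchers, nutritionists and participants are not blinded to the study group".

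That section gives the randomisation procedure to an independent statistician. Study timeline describes the step at the site: "After the baseline assessment, participants will be randomised to one of the three study groups done by the nutritionists"; the nutritionists also tell participants their group. The list of strengths and limitations says that the nutritionists collect the data on all outcomes.

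The article does not say how the next block is changed, in which stratum, or how many couples are expected.

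**The concern.** In an ordinary permuted block the composition is fixed in advance. Under the couples rule it depends on an event that the site has just observed. If a couple goes to arm A, arm A has one participant too many, and the next block must under-supply A. Staff who know the rule can discount A before they meet the next candidate.

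The staff concerned have room to act on this. Nutritionists conduct the dietary recalls that settle eligibility and the protein stratum. The baseline 400 m walk, a test of maximal sustained effort with encouragement each lap, is done before randomisation and is a covariate in the primary model. Foreseeable allocation could therefore influence who enters, when they enter, and how baseline is measured.

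Sex is a stratification factor, so an opposite-sex couple spans two strata. The article does not say which stratum's next block is corrected.

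**Working it through.** **Inputs from the article.** Three arms, 1:1:1, blocks of three; two protein levels by two sexes, giving 4 strata, or 8 if lists are kept per site; N = 264 (88 per arm); difference 28 s, SD 61 s, two-sided α = 0.05, power 0.8.

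**Assumed.** 5%, 10% or 20% of participants in couples; partners of opposite sex; correction applied in the second partner's stratum.

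**The plan's own figure.** n = 2 × (1.96 + 0.84)² × 61² / 28² ≈ 75 per group, as stated. With 15% drop-out, 225 / 0.85 = 264.7, against 264 stated. The article gives no figure for predictability.

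**Best-guess rate within a block** (observer knows the composition and past assignments):

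- Intact block A, B, C: (1/3 + 1/2 + 1) / 3 = 61.1%; one third of assignments certain.
- Couple's arm A left out (B, C): (1/2 + 1) / 2 = 75.0%; half certain; A has probability 0.
- Block kept at three places without A (B, B, C): (2/3 + [2/3 × 1/2 + 1/3 × 1] + 1) / 3 = 77.8%; 44.4% certain; A has probability 0. This also gives B a new surplus.
- Block of six less one A (A, B, B, C, C): 60.7%, against 56.1% for an intact block of six; A comes first with probability 1/5 = 20%.

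**Unconditional probability.** The couple's arm is itself random. With A left out when the couple is in A, the chance that the first place of the corrected block is A is 1/3 × 0 + 2/3 × 1/2 = 1/3.

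**Whole trial.** Couples: 0.05, 0.10 or 0.20 × 264 / 2 = 6.6, 13.2 or 26.4. Each produces one corrected block of two, so about 13, 26 or 53 assignments are affected. Simulated best-guess rate over assignments drawn from the lists, with the couple's arm left out of the next block (400 replicates):

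| In couples | 4 strata, uncorrected → corrected | 8 strata, uncorrected → corrected |
|---|---|---|
| 5% | 0.608 → 0.614 | 0.604 → 0.611 |
| 10% | 0.608 → 0.621 | 0.604 → 0.617 |
| 20% | 0.607 → 0.634 | 0.604 → 0.630 |

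Hand check at 10%: 26.4 / (264 − 13.2) × (75.0 − 61.1) ≈ 1.5 points, against 1.3 simulated.

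**What the correction gains.** Mean gap between largest and smallest arm in the same simulations:

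- Uncorrected, for 5%, 10% and 20%: 2.9, 3.8 and 4.9 participants (4 strata); 3.4, 4.2 and 5.5 (8 strata). The 95th percentiles run from 6 to 11.
- Corrected: 1.6 to 1.7 (4 strata) and 2.2 to 2.6 (8 strata).

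Variance of a two-arm contrast relative to 88 v 88, same total:

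- 84 v 92: (1/84 + 1/92) / (2/88) = 1.002.
- 82 v 94, a gap of 12: (1/82 + 1/94) / (2/88) = 1.005.

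If the surplus sits in the third arm, one contrast loses and another gains. With arms of 82, 88 and 94, averaging over the three pairs gives (1/82 + 1/88 + 1/94) / (3/88) = 1.003.

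Power at the planned effect is 80.3% for 75 v 75, 80.1% for 70 v 80 and 79.6% for 65 v 85.

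**The case against.** The strongest reply is that the rule does little harm and that its mechanics are not known. Several parts of that reply stand.

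- **Randomness and ratio.** A reader might infer that assignments after a couple are not properly random, or that 1:1:1 is broken. Neither follows. The order of the remaining arms can still be random, and each arm keeps an unconditional chance of 1/3. Only the conditional probabilities shift, as they do inside any permuted block.
- **Timing.** A reader might infer that the very next participant cannot receive the couple's arm. The rule acts on the next block. A block already open is completed first, and an arm missing there was simply used up in an ordinary block of three.
- **Knowledge.** The article does not say that site staff know the correction rule, the block boundaries or the stratum corrected. The independent statistician may hold the lists, with the nutritionists only carrying out the assignment, and concealment details may be in the full protocol.
- **Block size.** It is tempting to call the leak independent of block length. It is not: in a block of six the rise is from 56.1% to 60.7%, and the corrected block is slightly less guessable than the plan's ordinary block of three.
- **Adjustment.** The primary model includes baseline walk time, protein intake and sex, which limits bias from selective enrolment but does not remove it.
- **Outcome assessment.** Unblinded measurement is already acknowledged as a limitation and exists whatever is done about couples.

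What remains is that the article states a rule tying a block's content to an open allocation, in a trial where the staff who see that allocation also perform the next one. This is not an omission that a fuller document would supply.

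**Conclusion.** The point holds as one of conditional foreseeability. If the correction is completed within one block of three, the couple's arm is absent from that block and the best-guess rate there is 75–78% instead of 61%. Over the trial the rise is about 0.5 to 3 percentage points. That range rests on the assumed 5–20% of participants in couples, on leaving the couple's arm out of the next block in the partner's stratum, and on an observer who knows the rule, the boundaries and the stratum. With less knowledge, or a correction spread over more places, the rise is smaller.

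Most of the predictability comes from the fixed block of three, where a third of assignments are certain to anyone tracking a stratum, with or without couples. The correction adds to it for a gain in precision too small to matter, so the rule is worth removing although its harm is limited.

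**What to change.** 1. Delete the sentence on correcting the next block.
2. Randomise each couple as one unit, 1:1:1, from a separate concealed list per site prepared by the independent statistician.
3. Leave the individual lists unchanged when a couple enrols.
4. Replace the fixed block of three with larger, varying block sizes that are concealed from the sites. Without this step the main source of predictability stays.

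Cost: one extra list per site. Arms may differ by a few participants, raising the variance by about 0.5% or less for two arms with the same total. The simulated gaps are for deleting the correction alone; the separate couples list was not simulated. Couples lose stratification by protein intake and sex. This is largely offset because the primary model already adjusts for both, and each opposite-sex couple brings one man and one woman to its arm.

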### Study timeline

The first clinic visit starts with written informed consent, and when participants are eligible, the baseline assessment will be performed. The baseline assessment consists of questionnaires (frailty status, risk of sarcopenia, self-reported mobility limitations, QoL and healthcare costs) and measurements (physical function, muscle strength and body composition). See below ‘primary and secondary outcomes’ and ‘other measures’ for details on these assessments. An accelerometer will be attached to measure physical activity for 7 subsequent days.

After the baseline assessment, participants will be randomised to one of the three study groups done by the nutritionists and they will inform the participants in which group they are allocated to. Participants randomised to one of the two intervention groups will be invited for a consultation meeting at the clinic to receive their personalise d dietary advice, and personalised advice on optimising the timing of protein intake in close proximity of usual physical activity (intervention group 2 only). This will take place within 2 weeks after the baseline assessment since the personalised advice needs to be composed by the nutritionist. The baseline assessment is considered the start of the study period for participants of the control group, while the consultation meeting is considered the start of the study period for participants of the intervention groups.

One week prior to the 3-month follow-up visit, dietary intake will be assessed again by means of a combination of three food diaries and three 24-hour dietary recalls. The 3-month follow-up visit will take place at the clinic and includes measurement of BW, assessment of self-reported mobility limitations, risk of sarcopenia, QoL, healthcare costs and the accelerometer will be attached to measure physical activity for 7 subsequent days.

One week prior to the 6-month follow-up visit (final measurement), dietary intake will again be assessed by means of a combination of three food diaries and three 24-hour dietary recalls, which allows us to determine compliance to the dietary advice. The 6-month follow-up visit at the clinic includes all measurements performed during the baseline visit and the accelerometer is attached again to measure physical activity for the next 7 days. Finally, among participants of the intervention groups only, several questions regarding the appreciation and adherence of the intervention and participants’ intention to follow the dietary advice in the future will be asked in order to perform a process-evaluation. Figure 1 shows the study timeline and table 1 provides an overview of all measurements.

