Self-reported mobility limitations will be assessed by means of a questionnaire; ‘Because of your health, how much difficulty do you have walking 400 metre?’ and ‘Because of your health, how much difficulty do you have climbing 10 steps?’ Participants will respond using a 5-level Likert scale: ‘no difficulty’, ‘a little difficulty’, ‘some difficulty’, ‘a lot of difficulty’ and ‘unable to do the activity’. Mobility limitation is defined as two consecutive reports of having any difficulty walking 400 m or climbing 10 steps without resting due to a health or a physical problem.

QoL will be measured using the EuroQol 5D-5 L Questionnaire.^63^

Incident frailty will be assessed using the Fried criteria.^64^ Participants will be considered ‘frail’ when three or more components are present. Those with no components will be considered ’robust’, whereas those with one or two components will be considered ’prefrail’. The criteria include (1) self-reported unintentional weight loss (>4 kg in past 6 months), (2) self-reported exhaustion (based on two questions from the Center for Epidemiologic Studies Depression Scale on exhaustion in the past week at baseline and follow-up: ‘I felt that everything I did was an effort’ and ‘I could not get going’. Scores range from 1 ‘rarely or none of the time’ to 4 ‘always or most of the time’. A score of 3 or 4 on either question indicates exhaustion,^65^ (3) weakness (grip strength in the lowest 20% of the whole study population based on the mean of the maximum scores, adjusted for gender and BMI), (4) slow walking speed (walk time on the 4 m walk test in the slowest 20% of the whole study population, adjusted for gender and height), and (5) low physical activity (total counts per week based on the accelerometer data in the lowest 20% of physical activity for each gender). Incident frailty is considered deterioration of frailty status; that is, from robust at baseline to prefrail or frail at follow-up or from prefrail at baseline to frail at follow. Frail participants at baseline will be excluded from these analyses.

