#### Other measures

BW will be measured without shoes in underwear to the nearest 0.1 kg using a digital calibrated scale (Finland; SECA 877, the Netherlands; Marsden M-520). Body height will be measured to the nearest millimetre using a SECA stadiometer for mobile height measurements (Finland; SECA 217, the Netherlands; SECA 214). Corrections will be made to adjust the measured BW for clothing, shoes or a cast (minus 1 kg for each element), and to adjust the measured body height for shoes (minus 1 cm). Change in BW and BMI at 3 months and 6 months will be calculated. As the personalised dietary advice is isocaloric, no significant difference in BW or BMI is expected. Physical activity will be objectively assessed by means of an accelerometer (Axivity, AX3) during 7 subsequent days after each clinic visit (baseline, 3-month follow-up visit and 6-month follow-up visit). The accelerometer will be attached by a nutritionist to the frontal part of the right thigh in the midpoint between iliac crest and patella bone when sitting down, with a surgical plaster. Participants can perform any physical activity as the accelerometer is water resistant. Appetite will be measured with Simplified Nutritional Appetite Questionnaire.^68^ Dietary intake will be assessed by means of a combination of three food diaries and three 24-hour dietary recalls prior to the 3-month follow-up visit and the 6-month follow-up visit.

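### The protocol does not ensure that the 7-day baseline activity recording ends before participants learn their arm or receive the advice

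*Protocol article*

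**What the plan says.** All references are to the protocol article.

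- **Recording window.** At the baseline visit, "An accelerometer will be attached to measure physical activity for 7 subsequent days" (Study timeline). Other measures confirms that activity is recorded "during 7 subsequent days after each clinic visit (baseline, 3-month follow-up visit and 6-month follow-up visit".
- **Content of the baseline assessment.** The Study timeline lists questionnaires and "measurements (physical function, muscle strength and body composition". The accelerometer has its own sentence after that list.
- **Randomisation and disclosure.** "After the baseline assessment, participants will be randomised to one of the three study groups done by the nutritionists and they will inform the participants" (Study timeline). No day is given. Randomisation, allocation and masking states that participants, nutritionists and researchers are not blinded.
- **Advice.** For the consultation in the intervention groups: "This will take place within 2 weeks after the baseline assessment since the personalised advice needs to be composed by the nutritionist". No earliest day is given. The control group's study period starts at the baseline assessment.
- **Use of the recording.** Under Secondary outcomes, the fifth Fried criterion is "low physical activity (total counts per week based on the accelerometer data in the lowest 20% of physical activity for each gender". Incident frailty is a move to a worse class from baseline, and "Frail participants at baseline will be excluded from these analyses".

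**The concern.** A baseline value should be fixed before allocation can influence it. Here the baseline activity week starts at the visit and runs forward, and the text lets disclosure and advice fall inside that week. If unblinded participants become more or less active on learning their arm, the baseline week carries part of the response to allocation.

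Two analyses use that week. The first is change in physical activity. The Statistical analyses plan section treats other measures analogously to the primary outcome, which is adjusted for baseline. Adjusting for a baseline that already reflects allocation can absorb part of an early effect. The second is incident frailty, where the activity component helps set both the starting class and the exclusion of frail participants. A starting state or exclusion that allocation can influence weakens the randomised comparison for that secondary outcome.

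**Working it through.** The plan gives no figure on this point to reproduce. The check is the order of events, followed by a bound on what one frailty component can do.

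**1. Overlap in days.** Recording covers days 1 to 7 after the visit. If disclosure (or advice) falls on day d, the number of recorded days that follow it is max(0, 7 − d).

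| Day of disclosure or advice | Recorded days that follow it |
|---|---|
| 0 | 7 |
| 1 | 6 |
| 3 | 4 |
| 7 or later | 0 |

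Every row complies with the Study timeline. If consultation days were spread evenly over 0 to 14 (an assumption), 7/14 = 50% of intervention participants would receive advice before recording ends. On average 0.5 × 3.5 = 1.75 of the 7 days would follow the advice.

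**2. What the activity component can decide.** Robust means 0 components, prefrail 1 or 2, frail 3 or more. The activity component therefore settles the class when the other four sum to 0 (robust or prefrail) or to 2 (prefrail or frail, which is the exclusion). Weakness and slowness are defined as the worst 20%, so each is set at 0.20. The prevalence q of weight loss and of exhaustion is not given and is varied. Independence of the components is assumed.

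- P(sum 0) = 0.64(1 − q)²
- P(sum 2) = 0.04(1 − q)² + 0.64q² + 0.64q(1 − q)

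| q | P(sum 0) | P(sum 2): decides exclusion | Total: decides class |
|---|---|---|---|
| 5% | 57.8% | 6.8% | 64.6% |
| 10% | 51.8% | 9.6% | 61.5% |
| 20% | 41.0% | 15.4% | 56.3% |

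So this one component would settle the three-level class in over half of participants, but the exclusion in far fewer.

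**3. Illustration of size.** The shift in activity is an assumption, not a figure from the document. Suppose counts are roughly normal, one of three arms is shifted upwards by s SD over the whole week, and the 20% cut is taken on the pooled sample. The cut c then solves [2Φ(c) + Φ(c − s)]/3 = 0.20.

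| s | c | Flagged, shifted arm | Flagged, other arms | Gap per 88 |
|---|---|---|---|---|
| 0.10 | −0.809 | 18.2% | 20.9% | 2.4 |
| 0.25 | −0.764 | 15.5% | 22.2% | 5.9 |

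Multiplying by the shares in step 2 gives the between-arm difference per 88 participants:

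- Starting class: from 2.4 × 0.563 = 1.4 to 5.9 × 0.646 = 3.8 participants.
- Exclusion: from 2.4 × 0.068 = 0.2 to 5.9 × 0.154 = 0.9 participants.

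A smaller shift, or one covering only part of the week, gives proportionately less.

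**The case against.** The strongest reply is that the baseline assessment includes the recorded week. The accelerometer sentence stands in the paragraph that describes that assessment, the paragraph refers to Other measures for details, and Table 1 ticks accelerometers under the baseline visit. Figure 1, the timeline, is not available here. The consultation is also a separate meeting for which advice must first be composed, so days 8 to 14 comply fully. This stands to the extent that the text permits the overlap without requiring it. It does not close the gap. The listed content of the assessment omits the recording, the same assessment starts the control group's study period, and no sentence makes disclosure wait.

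Three stronger readings are tempting, and the document does not support them.

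- A reader might infer that baseline activity and baseline frailty are post-randomisation values. The day of randomisation is not stated, and only one of five frailty components is exposed.
- A reader might infer that group 2's timing advice changes the measure. The criterion uses total weekly counts. The Intervention section tells participants not to become more or less active, only to shift the moment, and shifting activity within the week leaves the total unchanged. What remains is a possible reaction to knowing the arm.
- A reader might object that at 6 months "the accelerometer is attached again to measure physical activity for the next 7 days", after the final visit. That window is the same in all arms and matches the other visits, so no differential bias follows. A posted, self-attached device at that visit alone would add a method difference.

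**Conclusion.** The point holds as a gap in procedure. The protocol does not keep disclosure and advice out of the baseline activity week, so baseline activity and the low-activity component of baseline frailty may be recorded after randomisation in unblinded participants.

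The size of any bias cannot be derived from the document. Under the assumed shifts of 0.10 to 0.25 SD, with normal counts and independent components, about 1 to 4 participants per 88 would differ between arms in starting class, and fewer than one in exclusion. The 400 m walk time, its baseline value, the stratification factors and the other four frailty components are untouched. Physical activity is listed among other measures, and the Discussion already concedes that frailty cases may be few. This is a cheap improvement to a secondary analysis and no threat to the main result.

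**What to change.** In the Study timeline, state that the allocation is disclosed and the consultation held only after the 7-day baseline recording is complete, that is on days 8 to 14, inside the existing 2-week limit. The cost is one sentence and some scheduling: allocation is announced about a week later, and the booking window for the consultation is shorter. No extra visit is needed.

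If participants are already enrolled, record for each one how many recorded days followed disclosure and how many followed the advice, and report this by arm. Repeat the incident-frailty analysis without the activity component as a sensitivity analysis. Leave the 6-month recording as it is.
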